## Abstract

**Objectives:**

The aim of the RAAS-COVID-19 randomized control trial is to evaluate whether an upfront strategy of temporary discontinuation of renin angiotensin aldosterone system (RAAS) inhibition versus continuation of RAAS inhibition among patients admitted with established COVID-19 infection has an impact on short term clinical and biomarker outcomes. We hypothesize that continuation of RAAS inhibition will be superior to temporary discontinuation with regards to the primary endpoint of a global rank sum score. The global rank sum score has been successfully used in previous cardiovascular clinical trials.

**Trial design:**

This is an open label parallel two arm (1,1 ratio) randomized control superiority trial of approximately 40 COVID-19 patients who are on chronic RAAS inhibitor therapy.

**Participants:**

Adults who are admitted to hospital within the McGill University Health Centre systems (MUHC) including Royal Victoria Hospital (RVH), Montreal General Hospital (MGH) and Jewish General Hospital (JGH) and who are within 96 hours of COVID-19 diagnosis (confirmed via PCR on any biological sample) will be considered for the trial. Of note, the initial protocol to screen and enrol within 48 hours of COVID-19 diagnosis was extended through an amendment, to 96 hours to increase feasibility. Participants have to be 18 years or older and would have to be on RAAS inhibitors for at least a month to be considered eligible for the study. Additionally, RAAS inhibitors should not have been held for more than 48 hours before randomization. A list of inclusion and exclusion criteria can be found in the full protocol document. In order to prevent heart failure exacerbation, patients with reduced ejection fraction were excluded from the trial.

Once a patient is admitted on the ward with a diagnosis of COVID-19, we will confirm with the treating physician if the participant is suitable for the RAAS-COVID trial and meets all the inclusion and exclusion criteria. If the patient is eligible and informed consent has been obtained we will collect data on sex, age, ethnicity, past medical history and list of medications (e.g. other anti-hypertensives or anticoagulants), for further analysis.

**Intervention and comparator:**

All the study participants will be randomized to a strategy of temporarily holding the RAAS inhibitor [intervention] versus continuing the RAAS inhibitor [continued standard of care]. Among participants who are randomized to the intervention arm, alternative guide-line directed anti-hypertensive medication will be provided to the treating physician team (detail in study protocol). In the intervention arm RAAS inhibitor will be withheld for a total of 7 days with the possibility of the withdrawn medication being initiated at any point after day 7 or on the day of discharge. The recommendation for re-initiating the withdrawn medication will be made to the treating physician. The re-initiation of these therapies are according to standard convention and follow-up as per Canadian guidelines. Additionally, the date of restarting the withdrawn medication or whether the medication was re-prescribed on discharge or not, will be collected. This will be used to conduct a sensitivity analysis. Furthermore, biomarkers such as troponin, c-reactive protein (CRP) and lymphocyte count will be assessed during the same time period. Samples will be collected on randomization, day 4 and day 7.

**Main outcomes:**

**Primary endpoint:**

In this study the primary end point is a global rank score calculated for all participants, regardless of treatment assignment ( score from 0 to 7). Please refer to table 4 in the full protocol. In the context of the current trial, it is estimated that death is the most meaningful endpoint, and therefore has the highest score ( score of 7). This is followed by admission to ICU, the need for mechanical ventilation etc. The lowest scores ( score of 1) are assigned to biomarker changes (e.g. change in troponin, change in CRP). This strategy has been used successfully in cardiovascular disease trials and therefore is applicable to the current trial.

The primary endpoint for the present trial is assessed from baseline to day 7 (or discharge). Participants are ranked across the clinical and biomarker domains. Lower values indicate better health (or stability). Participants who died during the 7th day of the study will be ranked based on all events occurring before their death and also including the fatal event in the score. Next, participants who did not die but were transferred to ICU for invasive ventilation will be ranked based on all the events occurring before the ICU entry and also including the ICU admission in the score. Those participants who did not die were not transferred to ICU for invasive ventilation, will be ranked based on the subsequent outcomes. The mean rank score will then be compared between groups. In this scheme, a lower mean rank score indicates greater overall stability for participants.

Secondary endpoints :

The key secondary endpoints are the individual components of the primary components and include the following: death, transfer to ICU primarily for invasive ventilation, transfer to ICU for other indication, non-fatal MACE ( any of following, MI, stroke, acute HF, new onset Afib), length of stay > 4 days, development of acute kidney injury ( > 40% decline in eGFR or doubling of serum creatinine), urgent intravenous treatment for high blood pressure, 30% increase in baseline high sensitivity troponin, 30% increase in baseline BNP, increase in CRP to > 30% in 48 hours and lymphocyte count drop> 30%. We will also look at the World Health Organization (WHO) ordinal scale for clinical improvement (in COVID-19) in our data. In this scale death will be assigned the highest score of 8. Patients with no limitation of activity will be assigned a score of 1 which indicates overall more stability (3).

Additionally, we will evaluate the potential effects of discontinuing RAAS inhibition on alternative schedules (longer/shorter than 7 days, intermittent discontinuation) using a mechanistic mathematical model of COVID-19 immunopathology calibrated to data collected from our patient cohort. In particular, we will assess the impact of alternative schedules on primary and secondary endpoints including increases to baseline CRP and lymphocyte counts.

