**Randomization:**

Participants will be randomized in a 1:1 ratio. Randomization will be performed within an electronic database system at the time of enrolment using a random number generator, an approach that has been successfully used in other clinical trials. Neither participant, study team, or treating team will be blinded to the intervention arm.

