**Blinding:**

This is an open label study with no blinding.

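### The primary score's window can close at discharge, which an unblinded team decides, so assessment time is unequal and can depend on the arm

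*Protocol article*

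**What the plan says.** Under Main outcomes, Primary endpoint, the protocol article sets the window: "The primary endpoint for the present trial is assessed from baseline to day 7 (or discharge"). It does not say whether the earlier or the later of the two dates applies. It gives no rule for an event after discharge but before day 7.

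On who knows the allocation, the Blinding section says: "This is an open label study with no blinding". The Randomization section is more specific: "Neither participant, study team, or treating team will be blinded to the intervention arm".

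The secondary endpoints paragraph supplies the items of the score: "The key secondary endpoints are the individual components of the primary components and include the following: death, transfer to ICU primarily for invasive ventilation". Further down the same list stands "length of stay > 4 days, development of acute kidney injury". Readmission is not on it.

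The Intervention and comparator section gives the sampling days: "Samples will be collected on randomization, day 4 and day 7". In the scoring, "death is the most meaningful endpoint, and therefore has the highest score ( score of 7"), and biomarker changes carry 1 point. The mean rank score is then compared between arms of about 20 participants each. Scoring details are referred to a table in the full protocol, which is not shown here.

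**The concern.** A primary endpoint should give every randomised participant the same opportunity to be scored. Here the length of that opportunity depends on discharge, which happens after randomisation, which treatment can influence, and which is decided by clinicians who know the arm. Fewer days in the window mean fewer days on which a clinical item can be recorded and fewer study samples on which a biomarker item can turn positive. Both lower the score, and a lower score is read as greater stability.

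If discharge timing differs between arms for any reason, including a clinician's comfort with one strategy, the score shifts towards the arm that discharges earlier, even when the two strategies are equivalent. With about 20 participants per arm, a few such cases could matter.

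**Working it through.** **1. The texts side by side.** The window ends at day 7 or discharge. The treating team is unblinded. A stay of more than 4 days is an item, so stays of 4 days or less are foreseen. Participants are randomised after admission, so a stay of 4 days or less, counted from admission, also ends within 4 days of randomisation. Discharge before day 7 is therefore part of the design.

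- If the earlier date applies, a participant discharged on day 3 is assessed for 3 days and ranked against others assessed for 7. Both post-baseline study samples (days 4 and 7) may be missing. Discharge between days 4 and 7 puts only the day 7 sample at risk.
- If the later date applies, participants with long stays are assessed beyond day 7 and collect extra time at risk.

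On either reading, assessment time depends on discharge.

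**2. The plan's own figures.** The article gives no figure on discharge timing or post-discharge events to reproduce. The sample size of about 40 is stated without alpha, power, effect size or event rates, so it cannot be re-derived. This point does not depend on it.

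**3. Illustration: component events outside the window.** All inputs except the 40 participants and the 7 days are assumptions: share discharged early f = 20% to 60%, discharge day d = 3 or 5, and 7-day risk of a scored event after discharge r = 2% to 10%.

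Risk in the uncovered days: p = 1 − (1 − r)^((7 − d)/7). Expected events missed: 40 × f × p. Chance of missing at least one: 1 − (1 − f × p)^40.

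| f | d | r | p | Expected missed | Chance of at least one |
|---|---|---|---|---|---|
| 20% | 5 | 2% | 0.0058 | 0.046 | 4.5% |
| 40% | 3 | 5% | 0.0289 | 0.462 | 37.2% |
| 60% | 3 | 10% | 0.0584 | 1.402 | 76.0% |

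Misses that are equal in both arms lose information. Misses that differ between arms bias the comparison.

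**4. Illustration: biomarker items.** Assume no true effect, items that add, and scoring from the study samples. Let the share discharged before the day 7 sample differ between arms by Δ = 10 to 30 percentage points. Let each of four 1-point items (troponin, BNP, CRP, lymphocytes) have a chance q = 10% to 30% of turning positive only at that sample. The spurious mean difference is 4 × q × Δ:

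- low: 4 × 0.10 × 0.10 = 0.04 points
- high: 4 × 0.30 × 0.30 = 0.36 points

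The CRP item is defined over 48 hours and may not depend on day 7. With three items, the range is 3 × 0.10 × 0.10 = 0.03 to 3 × 0.30 × 0.30 = 0.27 points.

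**5. One death.** Death carries 7 points. With about 20 per arm, one uncounted death lowers that arm's mean score by up to 7/20 = 0.35 points, if the points are averaged.

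**The case against.** The article is a summary. It refers scoring to a table in the full protocol, and rules for events after discharge are commonly left to such a document. Patients judged fit for discharge are plausibly at lower risk than those kept in, so few events may be lost; the low end of the illustration is negligible. Discharge also enters the score on purpose through the length-of-stay item, so not every difference linked to discharge is an artefact.

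Much of this stands, and it limits the point. A reader might go further in four ways that the document does not support:

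- **Post-discharge events are scored as no event.** The article does not say so. Such events fall outside the window on its natural reading, but how they are handled is not stated.
- **Readmissions are lost.** Readmission is not an item of the score, so a plain readmission would score nothing even in a fixed window.
- **Discharge before day 4 rules out every biomarker item.** The 48-hour CRP item implies an earlier value, and the article does not say that only the scheduled study samples may be scored.
- **The window contradicts the 7-day hold.** The hold uses the same two anchors, with "the possibility of the withdrawn medication being initiated at any point after day 7 or on the day of discharge", so hold and window run in parallel. The restart date is also collected for a sensitivity analysis, although that concerns treatment and does not repair the window.

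The objection does not remove the stated rule itself. The article fixes the window and ties it to discharge. The length-of-stay item already credits early discharge once; the shorter window lowers the score a second time, by giving the other items less time to occur.

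**Conclusion.** The point holds. As published, the primary window depends on discharge in an open-label trial. Assessment time is therefore unequal and can depend on the arm, and an arm difference in discharge timing can shift the score without a true effect. On the natural reading, death, ICU transfer or a major cardiovascular event between discharge and day 7 lies outside the window, and scheduled samples may be missing.

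The size cannot be computed from the article. The ranges above (0.05 to 1.4 missed events among 40; a spurious difference of 0.04 to 0.36 points) rest on assumed discharge shares, discharge days, event risks and biomarker probabilities. They show that the effect could be anything from trivial to important in a trial of this size. They do not show that bias occurred, or in which direction.

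**What to change.** - Define the primary window as randomisation to day 7 for every participant, regardless of discharge.
- Ascertain death, ICU transfer and major cardiovascular events to day 7 by record check or one telephone call for anyone discharged earlier.
- Keep all randomised participants in the ranking. Prespecify one rule, the same in both arms, for biomarker items not sampled because of discharge.
- Add a sensitivity analysis on the clinical components alone.

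Two shortcuts should be avoided. Ranking biomarkers only among those sampled selects on a post-randomisation event. Making discharge the best tier gives still more weight to an unblinded decision.

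The cost is a wording amendment and one contact or record check per early discharge: 8 to 24 participants if 20% to 60% of 40 go home early (40 × 0.20 = 8; 40 × 0.60 = 24). A call cannot recover laboratory items, which is why the rule for unsampled biomarkers and the sensitivity analysis are needed. The article describes the trial as still enrolling, so the change can be made prospectively for later participants and by record check for those already discharged.

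### The scoring rule for deaths conflicts with its own window and 0-7 range, and if prior events count it ranks an early death as healthier than a late one

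*Protocol article*

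**What the plan says.** All statements below are in the Protocol article, Main outcomes, Primary endpoint, unless noted.

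- Who is scored and on what range: "the primary end point is a global rank score calculated for all participants, regardless of treatment assignment ( score from 0 to 7".
- Weight of death: "death is the most meaningful endpoint, and therefore has the highest score ( score of 7".
- Weight of biomarker changes: "The lowest scores ( score of 1) are assigned to biomarker changes". Other weights are left to table 4 of the full protocol, which is not shown.
- Window: "The primary endpoint for the present trial is assessed from baseline to day 7 (or discharge".
- Rule for deaths: "Participants who died during the 7th day of the study will be ranked based on all events occurring before their death". The same sentence then counts the death itself: "also including the fatal event in the score".
- Rule for the next group: "participants who did not die but were transferred to ICU for invasive ventilation will be ranked based on all the events occurring before the ICU" admission, with that admission counted as well. The remaining group also consists of people who did not die.
- Direction: a lower value is better, and the mean rank score is compared between arms.

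Two other parts of the article matter. The list of components under Secondary endpoints includes a hospital stay of more than 4 days and several biomarker changes. The Intervention and comparator section schedules biomarker samples at randomisation, day 4 and day 7.

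**The concern.** Death is the top category of the primary endpoint, so its scoring rule should be the clearest one in the section. It has two problems.

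The first is wording. The sentence names deaths on day 7 only, and the two groups that follow both require survival. That does not agree with the window, the population or the score for death given in the same section.

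The second remains when the wording is read charitably. A participant who dies is placed according to what happened before death plus the death itself, and some of those earlier events need survival time. Someone who dies soon after randomisation has little chance of recording a long stay and no chance of reaching a day-4 or day-7 sample. If those events count, dying sooner gives a better score than dying later. An arm whose deaths came early would look healthier than one with the same number of later deaths. The arms hold about 20 people each, so a few deaths can affect the comparison. The trial is also open label, which is a further reason to fix the rule before anyone scores a participant.

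**Working it through.** The plan gives no figure of its own for this point. The only design number in the article is the approximate total of 40, and the argument does not depend on how it was derived. The check sets the stated rules side by side and then scores two deaths under each possible reading.

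**Step 1. Which rule covers a death on each day?**

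| Day of death | Death rule, read literally | ICU-ventilation rule (survivors) | Remaining rule (survivors) | Death rule, read as any death through day 7 |
|---|---|---|---|---|
| 1 to 6 | no | no | no | yes |
| 7 | yes | no | no | yes |

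The literal sentence omits days 1 to 6. Three other statements in the section cover those days: everyone is scored, death carries 7 with no day attached, and the window opens at baseline. Read consistently with them, the sentence means any death through day 7, and the gap closes.

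**Step 2. Early against late death, with every death admitted to the top category.**

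Inputs:
- Death = 7 and each biomarker change = 1 (both stated).
- Stay over 4 days = w. The article does not give w; it is assumed to lie between 1 and 6.
- Early case: death before day 4, no other event. No scheduled sample after randomisation has been reached, and no stay over 4 days is recorded.
- Late case: death on day 7, stay over 4 days, two biomarker changes.

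| Reading | Early death | Late death | Within 0-7? | Result |
|---|---|---|---|---|
| Events are summed | 7 | 7 + w + 1 + 1 = 10 (w = 1) to 15 (w = 6) | No | Early death ranks healthier |
| Deaths are ordered by prior events | 0 prior events | 3 prior events | Order cannot show in a score that stops at 7 | Early death ranks healthier |
| Worst event only, maximum 7 | 7 | 7 | Yes | Tie; the prior-events clause has no effect |

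The article does not say whether the stay is counted from admission or from randomisation. If counted from admission, an early death might also carry w. The early total is then 7 + w and the late total 7 + w + 2, so the direction is unchanged and the gap is 2.

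**Step 3. Size on the summed reading.**

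- Gap between the two deaths: 10 - 7 = 3 to 15 - 7 = 8 points (2 points if the long stay is common to both).
- Arm size: 40 / 2 = 20.
- Change in an arm's mean when one death is of the early rather than the late kind: 3/20 = 0.15 to 8/20 = 0.40 points lower, that is, apparently better (2/20 = 0.10 if the long stay is common to both).

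On the worst-event reading the change is 0.

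**The case against.** The strongest reply is that the section already settles the intent. It scores every participant, gives death the highest value whatever the day, and opens the window at baseline. The stated range also stops at 7, which argues against summation; under a worst-event score deaths simply tie. Table 4 of the full protocol may say how components combine, and the article describes itself as a summary.

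Much of this stands. A reader might infer from the day-7 wording that deaths on days 1 to 6 would be left out of the primary analysis. The documents do not support that: it takes one sentence read alone, against three statements beside it. A reader might also infer that the inversion will certainly occur. It depends on prior events being added or used to order deaths, and the article does not settle this. Nor should one conclude that survivors could outrank deaths on total points, because the section takes deaths first and other participants afterwards, which suggests separate tiers.

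The discharge point is also limited. The window is given as day 7 or discharge, without saying that the earlier applies or that a later death is ignored. That needs one clarifying sentence and is not evidence that such deaths are dropped.

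What the reply does not remove is the conflict inside the stated rule. Any prior event added to a death takes the total above 7, and the reading that keeps to the range makes the clause about prior events idle. Weights in table 4 would not reconcile these two statements.

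**Conclusion.** The point holds in limited form. The day-7 wording is most likely a slip, but it contradicts the section's own window, population and score for death and should be corrected. The clause that scores deaths on earlier events either ranks an early death as healthier than a late one and breaks the 0-7 range, or has no effect.

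On the summed reading the illustrative gap between an early and a late death is 3 to 8 points, or 0.15 to 0.40 points on the mean of an arm of 20 for each such death. This rests on the assumed weight of 1 to 6 for a long stay and on the two illustrative cases. On the worst-event reading the effect is nil. The sample size is not affected. The point warrants a change because it concerns the top category of the primary endpoint and costs almost nothing to settle.

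**What to change.** Replace the sentence on deaths with a rule that states:

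1. Any death from randomisation through day 7 takes the worst score, 7, the top of the stated range.
2. Deaths are tied, or an earlier death ranks worse; choose one in advance.
3. Non-fatal events before death neither add to the score nor order the deaths.
4. The lower tiers apply only to participants alive at the end of the window.
5. A known death by day 7 after an earlier discharge counts as a death.

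Check that table 4 of the full protocol agrees. The cost is a few sentences in the endpoint definition and, for people discharged before day 7, a note of vital status where it is known. The downside is that earlier events no longer separate participants who died, a negligible loss of information.

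### The stand-alone length-of-stay endpoint (more than 4 days) puts a patient who dies in hospital within 4 days in the favourable category, so the arm with more early deaths can look better on it

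*Protocol article*

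**What the plan says.** Under Main outcomes, the secondary-endpoint paragraph of the protocol article states: "The key secondary endpoints are the individual components of the primary components and include the following: death, transfer to ICU primarily for invasive ventilation". The list has eleven items: death and ten non-fatal ones. The non-fatal items are two kinds of ICU transfer, non-fatal MACE, length of stay, kidney injury, urgent intravenous blood-pressure treatment and four biomarker changes.

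The length-of-stay item reads in full "length of stay > 4 days". It does not mention discharge alive, and death is not part of it.

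The article handles death explicitly in other places:
- **Primary score.** Death takes the highest score, 7, and patients who die are "ranked based on all events occurring before their death and also including the fatal event in the score". The window is stated as follows: "The primary endpoint for the present trial is assessed from baseline to day 7 (or discharge").
- **WHO ordinal scale**, also a secondary outcome: "In this scale death will be assigned the highest score of 8".
- **Key secondary endpoints.** Death is the first item listed.

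The article gives no rule for classifying a patient who dies before a non-fatal component could occur. It refers to a full protocol, which is not shown.

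**The concern.** A short stay is a good result only if it ends in discharge alive. The item as defined does not separate the two ways a stay can end within 4 days. A patient who goes home on day 3 and a patient who dies on day 3 both fall in the category of 4 days or less, which is the favourable one. No coding convention has to be assumed to reach this; it follows from the definition.

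Inside the primary score this does little harm, because death carries the worst score and outweighs a missing length-of-stay point. Once the score is split and the item is reported on its own, that protection is gone.

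The primary score mixes death, clinical events and biomarker shifts, so readers will look to the component table to see what drives it. If one arm has more early deaths, its length-of-stay row can improve for that reason alone and point the wrong way.

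**Working it through.** **The plan's own figure.** The article gives no death rate, length-of-stay rate or expected component result, so there is nothing to reproduce on this point. Its total of about 40 patients, randomized 1:1, gives about 20 per arm, which is used below only to turn percentages into patients.

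**Inputs, all assumed.**
- *d*: share of an arm dying in hospital within the first 4 days of the stay.
- *q*: share of those alive at day 4 whose stay exceeds 4 days, taken as equal in both arms so that treatment has no real effect on stay among survivors.

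**Formulas.**
- Plain item as written: (1 − d) × q
- With early death counted as unfavourable: (1 − d) × q + d

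**Main illustration, q = 0.60.**

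| Early deaths d | Plain item | Death counted |
|---|---|---|
| 5% | 0.95 × 0.60 = 57% | 57% + 5% = 62% |
| 15% | 0.85 × 0.60 = 51% | 51% + 15% = 66% |
| 20% | 0.80 × 0.60 = 48% | 48% + 20% = 68% |

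Comparing 15% with 5%, the arm with more deaths looks better by 6 points on the plain item and worse by 4 points when death counts. Comparing 20% with 5%, it looks better by 9 points and worse by 6 points.

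**In patients, at 20 per arm.** Early deaths of 15% vs 5% are 3 vs 1. The plain item gives 10.2 vs 11.4 expected patients, a gap of 1.2. With death counted it is 13.2 vs 12.4, a gap of 0.8 the other way.

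**Range over q, early deaths 4/20 vs 1/20.**

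| q | Plain (more vs fewer deaths) | Death counted (more vs fewer deaths) |
|---|---|---|
| 0.2 | 16% vs 19% (−3) | 36% vs 24% (+12) |
| 0.4 | 32% vs 38% (−6) | 52% vs 43% (+9) |
| 0.6 | 48% vs 57% (−9) | 68% vs 62% (+6) |
| 0.8 | 64% vs 76% (−12) | 84% vs 81% (+3) |

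**Range over deaths, q from 0.2 to 0.8.** The false advantage on the plain item is q times the difference in d. It is 1 to 4 points for 2/20 vs 1/20, 3 to 12 points for 4/20 vs 1/20, and 5 to 20 points for 6/20 vs 1/20.

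**Direction.** With equal q, the plain difference is −q × (difference in d) and the difference with death counted is (1 − q) × (difference in d). For any q between 0 and 1 the signs are opposite.

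**The case against.** A reader might infer that an early death counts as event-free on all ten non-fatal components. The article does not support that:
- **No such rule is stated.** The paragraph lists endpoints without a denominator or a coding rule for deaths. That detail is commonly left to the full protocol or the SAP, and its absence from a condensed article is not a fault.
- **Clinical components.** For ICU transfer, MACE, urgent blood-pressure treatment and kidney injury ("development of acute kidney injury ( > 40% decline in eGFR or doubling of serum creatinine"), an event before death still counts. Only a death with no prior event is in question.
- **Biomarkers.** "Samples will be collected on randomization, day 4 and day 7". A patient who dies before day 4 would lack that value, which is missing data and not automatically a favourable result. Comparing only those sampled would select survivors, a separate question. The CRP and lymphocyte item, "increase in CRP to > 30% in 48 hours and lymphocyte count drop> 30"%, has a 48-hour window for CRP, and a death on day 2 does not by itself rule out a rise within it.

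A reader might also infer that excess deaths would be hidden. They would not be: they show in the primary score, in the separate death endpoint and in the WHO scale.

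Three further objections deserve weight. First, the article does not say whether the 4 days run from admission or from randomization. If they run from admission, a patient enrolled late (up to 96 hours after diagnosis) may already be near or past 4 days, and fewer deaths would be affected. Second, the rates are assumed, and a shift of about one patient in 20 is within chance. Third, recasting every component as component or death would repeat the same deaths in every row and blur the breakdown of the score.

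The first two limit the size of the problem, and the third limits the remedy. None changes what the length-of-stay item says: on either clock, an in-hospital death within the first 4 days of the stay falls on the favourable side.

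**Conclusion.** The point holds for the length-of-stay component. As defined, it classes an in-hospital death within 4 days as a favourable outcome, so an imbalance in early deaths pushes the comparison the wrong way. Under the assumed 60% rate among those alive at day 4 and early deaths of 15% vs 5%, the plain result is 51% vs 57% and the result with death counted is 66% vs 62%. Over the range examined the false advantage is 1 to 20 points; with an imbalance of a single early death per 20 it is 1 to 4 points, less than one patient.

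These sizes assume equal stay among survivors in both arms and death rates that the article does not supply. The defect in the definition depends on neither assumption.

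The point does not extend to the other nine non-fatal components as a stated error. It leaves the primary endpoint unaffected, and mortality remains visible. This is a minor but worthwhile improvement to one secondary endpoint.

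**What to change.** - **Length of stay.** Define the component as not discharged alive by day 4, that is, a stay of more than 4 days or an in-hospital death. Show the plain count of stays over 4 days beside it so that the link to the primary score remains visible.
- **Other non-fatal components.** Keep them as individual components. Beside each, show by arm the number of deaths without a prior event of that component. Component or death can be added as a supportive analysis at most.
- **Death.** Leave it as its own key secondary endpoint.

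The cost is a change of wording and one extra column in the secondary-endpoint table. No new data or patients are needed, and the primary endpoint is unchanged. The small downside is a length-of-stay rate slightly less specific to time in hospital, which the plain count beside it offsets.
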